***Hypotheses***

Regarding the first aim, it is hypothesized that both the crisis plan facilitated through the patient’s advocate and by the clinician can reduce the number of psychiatric emergency visits and (involuntary) admissions as compared to the control group without a crisis plan. In addition, we expect a greater effect when the crisis plan is facilitated through the patient’s advocate as compared to the crisis plan developed with the clinician only. Furthermore, we expect greater effects on the patient’s satisfaction with treatment and psychological functioning when the crisis plan is facilitated through the patient’s advocate as compared to the crisis plan developed with the clinician only. Another aim of this study is to investigate the mediating mechanisms of the crisis plan. The expectation is that after creating the crisis plan, patients will show improvements in working alliance, insight into illness, self-efficacy, therapy adherence, acceptance of the illness and social support (see figure 1)**.**

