***Recruitment/procedure***

Candidate participants are selected from the clinicians’ caseloads by the clinician and the researcher. The selected patients receive an information letter about the study from their clinicians, who request the patient’s permission to be contacted by an independent researcher. The researcher explains the research goals and randomisation procedure. After providing written informed consent, the baseline interview follows.

The second interview with the patient is scheduled nine months later, and the last interview eighteen months after the baseline measurement.

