***Secondary outcome measures***

Secondary outcome measures include health and social functioning, the patient’s influence on crises situations and treatment satisfaction.

*Health and social functioning*

This is assessed by an independent interviewer using the Dutch version of the Health of the Nation Outcome Scales [13, 14]. The HoNOS form is completed by the researcher after a structured interview to quantify the health and social problems during the previous two weeks. Twelve items refer to behavioural problems, impairment, symptoms and social (dis)functioning. Three HoNOS-addendum items refer to manic symptoms, treatment motivation and compliance with medication. The items are rated from 0 (no problem) to 4 (severe to very severe problem)

*Evaluation of Crisis Plan (ECP)*

The patient’s opinion regarding the quality of the crisis plan's creation process will be assessed using a newly developed 13-item self-report *Evaluation of Crisis Plan* questionnaire. Specifically, the patient is asked whether he or she feels that the crisis plan reflects his or her wishes about what to do during a crisis. The items are rated on a 5 point scale, from 0 ‘no, I strongly disagree’ to 4 ‘yes, I strongly agree’.

*Mental Health Care Thermometer (MHC-T)*

Treatment satisfaction is measured according to the *Mental Health Care Thermometer* [15, 16]. The 16 items on this scale consist of “yes” or “no” categories that refer to the patient’s satisfaction regarding the treatment information received, the patient’s involvement in the treatment planning, the patient’s impression of the clinician and of the treatment quality.

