***Power***

The difference for the primary outcome variable between the intervention groups and the control group is based on a power of 0.90 and an alpha of 0.05. To detect an effect size of 0.6, each condition requires a minimum of 50 subjects. We have decided to use 80 subjects in each group to make up for those that we anticipate will be lost in the follow-ups.

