***Statistical analyses***

Analysis will be performed according to the *intention-to-treat* principle. Group difference will be investigated by chi-square tests and an(c)ova.

A patient is an study completer when he or she has completed all three interviews. After the intention to treat analyses, we will also analyse the effects in those patients who have completed the crisis plan. The missing data of secondary and mediating variables will be replaced by the data of the last available measurement using the principle of *last observation carried forward*

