**Table 1: Instruments at three research contacts**

**M1 Baseline M2 9 months M3 18 months**

**WAI** X X X

**PI** X X X

**CC** X X X

**MHC-T** X X X

**ECP** X

**RSQ** X X X

**MASERY** X X X

**SERVES** X X X

**ASR** X X X

**HoNOS** X X X

WAI: *Working Alliance Inventory*, PI: *Psychosis Insight*, CC: *Coping with Crisis*, MHC-T: *Mental Health Care Thermometer*, ECP: *Evaluation of Crisis Plan*, RSQ: *Recovery Style Questionnaire*, MASTERY: *Control of one’s life events*, SERVES: *Service Engagement Scale*, ASR: *Adult Social Report*, HoNOS: *Health of the Nation Outcome Scale*.

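### Last observation carried forward, the only stated rule for missing secondary and mediator scores, can bias those effects and leave their 95% intervals with less than nominal coverage

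*Protocol*

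**What the plan says.** Protocol, Statistical analyses, sets three things that act together:

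- The population: "Analysis will be performed according to the *intention-to-treat* principle".
- The tests: "Group difference will be investigated by chi-square tests and an(c)ova".
- The rule for gaps: "The missing data of secondary and mediating variables will be replaced by the data of the last available measurement", named there as last observation carried forward (LOCF).

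Recruitment/procedure gives the timing: "The second interview with the patient is scheduled nine months later, and the last interview eighteen months after the baseline measurement". Table 1 ("Instruments at three research contacts") shows every scale at all three visits except the Evaluation of Crisis Plan (ECP), which is taken once.

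Hypotheses states that after the plan is made "patients will show improvements in working alliance, insight into illness, self-efficacy, therapy adherence, acceptance of the illness and social support". Power raises the group size from 50 to 80 "to make up for those that we anticipate will be lost in the follow-ups". No dropout rate is given.

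**The concern.** LOCF assumes that a patient who leaves stays at the last recorded score. Here the gap is 9 months for someone seen at M2 and 18 months for someone seen only at baseline. This conflicts with the protocol's own hypothesis that the mediators move after the plan is made. A patient lost before M2 enters with a score from before randomisation, so the change in each mediator is zero by construction. Under intention to treat, these filled-in values go into the ANCOVA as if they had been observed.

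Two results are at stake. The second aim (locus of control, social and psychological functioning) and the third aim (mediating mechanisms) rest on these scales. Mediation is the more exposed. Primary outcomes come from administrative and emergency-service systems, so a lost patient can have a real admission count paired with a mediator score frozen before the plan. That weakens the estimated link from plan to mediator.

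**Working it through.** **1. The plan's own figures.** Power gives 50 needed and 80 enrolled per group. The room for loss is 1 - 50/80 = 37.5%, and 80 x (1 - 0.375) = 50. This is an allowance for the primary outcome, not a stated dropout rate. The 50 itself is close to a one-sided calculation (48 for effect size 0.6, power 0.90, alpha 0.05). The two-sided figure is 59, which leaves room for 1 - 59/80 = 26%. A range of 20% to 37.5% is therefore used.

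**2. Assumptions (not in the protocol).** 80 per arm, SD 1, correlation 0.5 between visits, ANCOVA on baseline. Half of the lost patients miss M2 and M3, and half miss only M3. Half of any effect or trend is present at M2.

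**3. Shrinkage of a real effect.** Let d be the effect at M3 and p the loss in the intervention arm. Patients lost before M2 lose all of d, and those missing only M3 lose d/2. The expected bias is -p x d x (0.5 x 1 + 0.5 x 0.5) = -0.75 x p x d.

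| Effect d | Loss p | Bias |
|---|---|---|
| 0.6 SD | 20% | -0.75 x 0.20 x 0.6 = -0.09 SD |
| 0.6 SD | 37.5% | -0.75 x 0.375 x 0.6 = -0.17 SD |
| 0.3 SD | 20% | -0.75 x 0.20 x 0.3 = -0.045 SD |
| 0.3 SD | 37.5% | -0.75 x 0.375 x 0.3 = -0.084 SD |

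Simulation gives the same -0.09 and -0.17 SD for the 0.6 SD effect. Unequal dropout is not needed for this; an effect that grows after the carried value is enough.

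**4. Coverage and standard error (simulated, d = 0.6).** Coverage of the 95% interval is about 90% at 20% loss and 73-77% at 37.5% loss. ANCOVA on observed scores has bias of about zero and coverage of 94-95%. At 37.5% loss the LOCF standard error is 0.130 to 0.138. The observed data give 0.174, and a trial with nothing missing gives 0.137. The LOCF standard error does match the sampling spread of the LOCF estimate (0.130 v 0.131).

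**5. False difference from unequal loss (no true effect).** With a common change t, the expected bias is 0.75 x t x (difference in loss). Its sign depends on the direction of change and on which arm loses more.

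- Loss 37.5% v 20%, t = 0.3 SD: 0.75 x 0.3 x 0.175 = 0.04 SD. If all losses precede M2: 0.3 x 0.175 = 0.05 SD. Type I error is 6-7%.
- Loss 25% v 50%, t = 0.5 SD: 0.75 x 0.5 x 0.25 = 0.09 SD. Type I error is about 11%.

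**6. The case with no harm.** With no effect, no trend and equal loss, the simulated bias was nil.

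**The case against.** Much can fairly be said in the plan's defence, and several stronger readings that a reader might infer do not stand.

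- **That bias is certain.** It is not; step 6 shows a case without it. Nor does recruitment after a crisis guarantee drift. Participants/Setting allows the crisis to lie anywhere in the previous two years, and the patients are current outpatients. Change is plausible, and for the mediators the protocol itself predicts it.
- **That the intervals are too narrow as a second, separate defect.** The standard error is right for the LOCF estimator. The intervals miss the true value mainly because they are off-centre. What remains is that the standard error claims nearly complete-data precision.
- **That the effect falls to 62.5% of its true size.** That needs all 37.5% to be lost before M2 (1 - 0.375). Anyone seen at M2 carries forward a score taken after randomisation.
- **That dropout will differ by arm.** Nothing in the protocol predicts it, and Ethical principles lets control patients have a plan if they ask. The false difference is also modest: 0.04 to 0.05 SD is less than half a standard error.
- **That the rule gives a wrong result for ECP.** With a single measurement there is nothing to carry, so the score simply stays missing. This needs a clarifying line and is not an error in a result.
- **That every scale depends on the patient's interview.** Service engagement and one form of the working alliance are rated from the clinician's perspective, so they need not be lost with the patient.

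The 0.6 SD effect is borrowed from the primary sample-size calculation, which is why 0.3 SD is shown beside it. None of this supports LOCF as the only rule.

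**Conclusion.** The concern holds as a possible bias, confined to the secondary and mediator analyses. If an effect develops after the carried value, LOCF pulls it towards zero. For a 0.6 SD effect this is about 15% of the effect at 20% loss (0.09/0.6) and 28% at 37.5% loss (0.17/0.6). If scores change over time and loss is unequal, the bias can go either way, so the rule cannot be defended as conservative. That LOCF is a poor sole rule here does not depend on exact figures. The sizes do: they rest on the assumed loss, correlation, effect and timing of dropout.

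A reader might infer that the trial's main conclusion is threatened. The protocol does not support that, because the rule names only secondary and mediating variables and the primary outcomes are taken from records. The plan should be changed, but this is not a fatal flaw.

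**What to change.** Replace the LOCF sentence in Statistical analyses as follows.

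- **Repeated scales:** a likelihood-based mixed model on all observed visits, with group by visit and team. Use either M2 and M3 as outcomes with M1 as covariate, or M1, M2 and M3 as outcomes with no baseline covariate. M1 must not stand on both sides.
- **Mediation analyses:** multiple imputation by arm is an alternative.
- **Assumption to state:** both methods are valid if data are missing at random.
- **LOCF:** at most a sensitivity analysis.
- **ECP:** state that it is analysed on observed responses, among patients for whom a plan was made, with the number missing reported.

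The cost is a change of wording, slightly more analysis work, and larger standard errors that reflect the data actually observed. No new data are needed.

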***Ethical principles***

The study protocol, information brochure and informed consent form were approved by the Dutch Union of Medical-Ethic Trail Committees for mental health organizations (registration number 7.109, CCMO-nr NL 16818.097.07)

The effects of a crisis plan are unknown at this moment and therefore we think it is justified to allocate the participants randomly over the three conditions.

The clinician informs the patient about the research. After permission is granted, the interviewer informs the patient of the research aims and randomisation method and asks for his or her written informed consent. The patient is free to refuse participation at any time during the research period, without having to disclose any reason why.

Participants allocated in the control group receive care according to standard practice, without the creation of a crisis plan. In case patients in the control group wish to create a crisis plan, this will be honoured at any time during the research period.

The collected patient data are treated according to the Medical Confidentiality Rules, and are kept in locked files cabinets. Access is limited to members of the research group and the medical ethical committee.

***Discussion***

The central research question in this study is whether either of the two crisis plan types can reduce the use of psychiatric emergency services, as well as the number and duration of (involuntary) admissions. The secondary research question is whether the intervention improves psycho-social functioning. The identification of the possible intervention mediating mechanisms offers a tool for use in the development of future preventive interventions. The comparison between the two crisis plan types provides insight into the question whether a crisis plan facilitated through the patient’s advocate is more effective than a crisis plan facilitated through the clinician only. The study has several limitations and strengths.

*Limitations*

Firstly, no structured diagnostic interview is used to confirm the DSM-IV diagnosis. We decided to use the clinical diagnosis as derived from the medical records because of the extensive nature of the interview, and because a structured diagnostic interview-derived DSM-IV diagnosis is of limited importance in the present study. The second limitation is the possible recruitment bias. Because of the ethical consideration the clinician is the first person who informs the patient of the study. Some clinicians may have preferences for some patients to participate in the study. There is some risk that it will not be possible to generalise the results based on the expected response of about forty percent of the participants [7, 8]. People who don’t want to participate may have experienced a compulsory admission in the past and feel demoralized and disempowered.

*Strengths*

Important strengths are the clinical relevance and design of this study. Although crisis plans are formally part of the treatment plans, in practice clinicians rarely use advance statements. The structure and supervision provided by this study will help participating clinicians to switch their working method into a more structured and preventive approach.

The participants are not screened for their ability to make a crisis plan and therefore represent a more general population of patients with psychotic and bipolar disorders than a selected group of patients. Besides that, the multisite character of this study may also increase the generalization of the results. Internal validity is protected by the structured protocol monitoring and supervision of the clinicians.

This study is jointly developed and conducted with the patient’s advocacy group and, to our knowledge, is therefore the first randomised controlled trial which examines such an intervention.

***Competing interests***

The authors declare that they have no competing interests.

**Table 1: Instruments at three research contacts**

**M1 Baseline M2 9 months M3 18 months**

**WAI** X X X

**PI** X X X

**CC** X X X

**MHC-T** X X X

**ECP** X

**RSQ** X X X

**MASERY** X X X

**SERVES** X X X

**ASR** X X X

**HoNOS** X X X

WAI: *Working Alliance Inventory*, PI: *Psychosis Insight*, CC: *Coping with Crisis*, MHC-T: *Mental Health Care Thermometer*, ECP: *Evaluation of Crisis Plan*, RSQ: *Recovery Style Questionnaire*, MASTERY: *Control of one’s life events*, SERVES: *Service Engagement Scale*, ASR: *Adult Social Report*, HoNOS: *Health of the Nation Outcome Scale*.

**Figure 1**

**Figure of the mediator variables of the effects of the crisis plan.**

Crisis Plan

Increased quality of working alliance

Increased insight into the illness

Increased self efficacy

Increased therapy adherence

Increased acceptence of the illeness

Increased influence on the treatment and treatment satisfaction

Increased health and social functioning

Increased soal support

Reduction of the number of outpatient mental health emergency visits and of the number and duration of (compulsory) admissions

**Figure 2**

**Participant flowchart**. PACP: Patient’s Advocate facilitated Crisis Plan, CCP: Clinician facilitated Crisis Plan.

Selected for eligibility (n= )

Did not meet criteria for inclusion (n= ) Refused to participate (n= )

Not contacted (n= )

Other reason (n= )

Randomisation (n= )

Allocated to CCP (n= )

Received intervention (n= )

Did not receive intervention (n= )

For reason:

Allocated to control group (n= )

Allocated to PACP (n= )

Received intervention (n= )

Did not receive intervention (n= )

For reason:

Lost to follow-up (n= )

For reason:

Discontinued intervention (n= )

For reason:

Analysed (n= )

Excluded for analysis (n= )

For reason:

Analysed (n= )

Excluded for analysis (n= )

For reason:

Analysed (n= )

Excluded for analysis (n= )

For reason:

Lost to follow-up (n= )

For reason:

Discontinued intervention (n= )

For reason:

Lost to follow-up (n= )

For reason:

Discontinued intervention (n= )

For reason:
